## Abstract

**Introduction:**

Resistant hypertension is inadequately controlled blood pressure (BP) despite treatment with at least three BP-lowering drugs. A popular hypothesis is that resistant hypertension is due to excessive Na^+^-retention, and that ‘further diuretic therapy’ will be superior to alternative add-on drugs.

**Methods and analysis:**

Placebo-controlled, random crossover study of fourth-line treatment when added to standard (A+C+D) triple drug therapy: ACE inhibitor or Angiotensin receptor blocker (A) +Calcium channel blocker (C)+Diuretic (D). Patients (aged 18–79 years) with clinical systolic BP≥140 mm Hg (135 mm Hg in diabetics) and Home BP Monitoring (HBPM) systolic BP average ≥130 mm Hg on treatment for at least 3 months with maximum tolerated doses of A+C+D are randomised to four consecutive randomly allocated 12-week treatment cycles with an α-blocker, β-blocker, spironolactone and placebo. The hierarchical coprimary end point is the difference in HBPM average systolic BP between (in order) spironolactone and placebo, spironolactone and the average of the other two active drugs, spironolactone and each of the other two drugs. A key secondary outcome is to determine whether plasma renin predicts the BP response to the different drugs. A sample size of 346 (allowing 15% dropouts) will confer 90% power to detect a 3 mm Hg HBPM average systolic BP difference between any two drugs. The study can also detect a 6 mm Hg difference in HBPM average systolic BP between each patient's best and second-best drug predicted by tertile of plasma renin.

**Ethics and dissemination:**

The study was initiated in May 2009 and results are expected in 2015. These will provide RCT evidence to support future guideline recommendations for optimal drug treatment of resistant hypertension.

**Trial registration number:**

Clinicaltrials.gov NCT02369081, EUDract number: 2008-007149-30.

Strengths and limitations of this study
Randomised, masked, adequately powered study of rigorously defined resistant hypertension;Rigorously characterised population of patients with resistant hypertension.Use of home blood pressure monitoring to evaluate the blood pressure response to treatment.The trial is not powered to detect the impact of drug treatment on morbidity and mortality.Spironolactone is not licensed for the treatment of hypertension in UK.

## Introduction

Many patients treated for hypertension do not achieve their target blood pressure, defined according to most guidelines as a seated clinic blood pressure (BP) <140/90 mm Hg. There are various reasons for poor BP control, including clinical inertia in up-titrating therapy and poor patient concordance with treatment. There are also patients who appear to be genuinely resistant to drug treatment, hence the term ‘resistant hypertension’.^1^ Resistant hypertension has been defined in various ways, but recent international guidelines have moved towards a consensus that resistant hypertension is best defined as poor BP control despite treatment with at least three BP-lowering medications, one of which should be a diuretic.^2^
^3^ The recent National Institute for Health and Care Excellence (NICE) guideline was even more prescriptive by defining resistant hypertension as a blood pressure that is not controlled to recommended treatment targets despite treatment with maximal recommended or best tolerated doses of three specific drug types, that is, A+C+D, according to the NICE hypertension treatment algorithm, where ‘A’ is an **A**CE-inhibitor or **A**ngiotensin receptor blocker (ARB), ‘C’ is a **C**alcium channel blocker (CCB) and ‘D’ is a thiazide/thiazide type diuretic.^4^
^5^ Thus, when referring to the drug treatment of resistant hypertension, guidelines are specifically referring to fourth-line drug treatment, usually added to treatment with A+C+D.

With regard to drug treatment of hypertension, a ‘rule of thirds’ seems to apply, with approximately one-third of hypertensive patients achieving BP control with a single drug, one-third requiring two drugs and one-third requiring three drugs or more. Some of those requiring three drugs or more will be controlled with three drugs, with most surveys suggesting that approximately 10% of patients will require more than three drugs to control BP, and thus are defined as patients with resistant hypertension.^1^
^6^ The true prevalence of resistant hypertension has been poorly defined, but based on the aforementioned assumptions the prevalence in the UK alone would exceed 1 million people.

The choice of fourth-line drug treatment for resistant hypertension has been entirely empirical. This reflects the lack of data from randomised controlled trials directly comparing different drug treatment options for resistant hypertension; consequently, there remains real clinical uncertainty about the preferred clinical management of such patients. It is possible that it makes no difference what drug is added as fourth-line treatment and that the response, on average, will be the same for all available treatment options. Alternatively, it is possible that one class of drug will usually be superior to all the others because there is a common mechanism underpinning resistant hypertension for the majority of patients. In this regard, a popular view is that resistant hypertension is predominantly due to excessive sodium retention and thus ‘further diuretic therapy’ will usually be the most effective treatment.^3^
^7^ A third possibility is that resistant hypertension is a more heterogeneous state and that the study of average responses in cohorts in clinical studies masks substantial individual patient differences and that treatment decisions could potentially be better stratified.

With regard to treatment stratification, one approach would be to use biomarkers of the patient's sodium/volume status, the rational being that an excess of total body sodium would contribute to treatment resistance and could help define the best treatment for patients with resistant hypertension. In this regard, plasma renin level is a surrogate for and inversely related to sodium status.^8^ This may be especially true in patients already receiving treatment with A+C+D, all of which would be expected to increase plasma renin levels. In this setting, we hypothesised that the finding of low plasma renin (lowest tertile) would be strongly suggestive of excessive sodium load as a mechanism for resistant hypertension and thus, might predict that the best treatment response would be obtained with further diuretic therapy as the preferred fourth-line treatment. Conversely, the finding of an elevated plasma renin (highest tertile) would point to a better response to a drug that suppresses plasma renin, that is, a β blocker, whereas those in the mid-tertile of plasma renin would respond best to a α-blocker as fourth-line treatment.

We selected spironolactone as the ‘further diuretic’ therapy to be tested because of observational data suggesting its efficacy in lowering BP in resistant hypertension.^9–11^ However, the downside with spironolactone is the development of gynaecomastia in some patients with prolonged usage.^9^ A previous crossover comparison of diuretics showed that a potential alternative to spironolactone in this setting is amiloride.^12^ Thus, PATHWAY-2 will obtain prospective, sequential comparative evidence for amiloride in resistant hypertension by offering this treatment as an open-label run-out to all patients after completion of the prospective randomised treatment cycles, at doses likely to have comparable efficacy to the doses of spironolactone. The PATHWAY 2 study was initiated in May 2009, and the final results are expected in 2015. This manuscript describes the objectives, design and respecified analysis plan for the PATHWAY 2 study.

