#### Run-out phase of the study

To evaluate if amiloride would be a suitable alternative to spironolactone, the run-out phase of the study was used to evaluate the BP-lowering effectiveness of amiloride using an open label design. Patients were eligible for the amiloride open label run-out phase of the study as long as they did not develop potassium levels ≥5.5 mmol/L during the study treatment cycles. If eligible, patients were prescribed open-label amiloride 10 mg once daily for 6 weeks, followed by forced titration to amiloride 20 mg once daily for a further 6 weeks. Patients were evaluated at study sites at 6 and 12 weeks, and BP recorded in accordance with procedures for the main study. In the remaining patients, physicians will choose the exit drug based where possible on pretrial experience of fourth and fifth-line treatment. For patients with uncontrolled BP at the end of the treatment cycles, or the amiloride run-out phase, it was considered unethical to wait for completion of the overall study before their best treatment option could be revealed. Thus, at the end of the main study, the data base will be locked for individual patients and the data centre can reveal the best treatment option for an individual patient at the request of the study site PI. The full schedule of assessment and procedures is shown in the table 1.

**Table 1 BMJOPEN2015008951TB1:** PATHWAY 2 Study schedule and procedures

	Screening	Randomisation	Phase 1		Phase 2		Phase 3		Phase 4	
	Week −4	Week 0	Week 6	Week 12	Week 18	Week 24	Week 30	Week 36	Week 42	Week 48
Informed consent	X									
Medical history	X	X								X
Clinical examination	X									X
Concomitant medications	X	X	X	X	X	X	X	X	X	X
Weight	X	X	X	X	X	X	X	X	X	X
Inclusion/exclusion criteria check	X	X								
Clinic BP and heart rate	X	X	X	X	X	X	X	X	X	X
Home BP and heart rate*		X	X	X	X	X	X	X	X	X
Home BP 6 h after witnessed administration of A+C+D medication†		X								
12 lead ECG	X									X
PEFR	X	X	X	X	X	X	X	X	X	X
Blood tests—electrolytes, urea, creatinine	X	X	X	X	X	X	X	X	X	X
Blood tests—glucose, lipids, uric acid, Ca++	X									X
Blood tests—cholesterol, HDL and triglycerides		X								X
Blood tests –plasma renin/aldosterone‡		X								
Pharmacogenetics§		X								
Blood tests—haematology, albumin, glucose	X			X		X		X		X
Blood—serum ace levels		X								
24 h urinary electrolytes		X								
Urinalysis	X	X		X		X		X		X
HCG testing pregnancy	X	X		X		X		X		

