### Statistical analysis plan

The study has a hierarchical coprimary end point which will be the difference in the home systolic BP between spironolactone and placebo, followed by the difference in home systolic BP between spironolactone and the average of the other two active drugs, (doxazosin and bisoprolol), followed by the difference in home systolic BP between spironolactone and each of the other two active drugs. For secondary analyses, similar analyses of the primary analysis will be made using clinic blood pressure. We will also compare the proportion of patients achieving target blood pressure (home and/or clinic) with each of the three active treatments. We will examine the proportion of patients controlled by each drug who are also controlled by the run-out treatment, amiloride. We will look at the direction of correlation between plasma renin and the blood pressure response to each drug. We will then describe differences between blood pressure response to each drug at extremes of plasma renin. Similar analyses will be performed for each haemodynamic variable. We will also examine the predictive value of the baseline measurements of cardiac output, systemic vascular resistance and thoracic impedance. The study will also explore the cost-benefit of using plasma renin to stratify best treatment in individual patients. An additional end point will be analyses of relationships between genetic factors and pharmacodynamic responses.

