#### Statistical model

The protocol requires patients to take triplicate morning and evening HBPM BP readings for the 4 days before each study visit, a total of 24 readings per visit. We shall use the arithmetic mean of last 18 measurements prior to a study visit to calculate home blood pressure. If more than 18 measurements have been obtained, the earliest recorded readings will be discarded. Thus, for most patients we will use all the readings on days 1 to 3 prior to the visit, but if any of these are missing then readings from day 4 will be used instead. The minimum number of measurements required for a valid assessment of home blood pressure using home BPM is six. Means of the morning and evening readings will be used in all subsequent analysis.

We shall use a mixed model to analyse HBPM BP, with unstructured covariances for the repeated measures for a patient. The model will include terms for time of day (morning or evening), gender, age, height, weight and smoking history. We will also adjust for baseline BP. If any of the baseline BPs cannot be estimated, we will substitute the overall mean baseline value, set an indicator variable to denote an imputed value and include the indicator variable in the model. The model will also include terms for treatment and phase (to allow for period effects), and an indicator variable to identify the subgroup of patients whose crossover treatments were unblinded.

*The primary analysis* will use BPs recorded for the maximum tolerated dose of each drug. The first of the primary end points is the mean difference between spironolactone and placebo; the second is the mean difference between spironolactone and the average of other active treatments; and the third and fourth are the mean differences between spironolactone and each of the other active treatments taken individually.

*The secondary analysis* will estimate for each treatment: changes in home BP; clinic BP on maximum tolerated dose, and changes in clinic BP; responder rates; withdrawals due to adverse events; and haemodynamic variables and pulse wave analyses. We shall use mixed models to analyse the continuous variables and these will include baseline covariates.

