### Evaluating further diuretic therapy

Since spironolactone has been associated with the development of gynaecomastia, estimated to occur in approximately 6% of patients,^9^ we also incorporated an open label run-out phase for the study during which patients will be treated with amiloride, a potassium-sparing diuretic, to determine if this replicates the effects of spironolactone on BP, thus providing an alternative further diuretic therapy for those intolerant of spironolactone.

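### Amiloride is given only in an open-label run-out after all four randomised cycles, so its effect cannot be separated from a fifth phase, and the run-out cannot by itself show that amiloride replicates spironolactone

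*Protocol article*

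**What the plan says.** **Design.** Under Study design, patients are randomised with equal probability to one of 24 sequences of spironolactone, doxazosin, bisoprolol and placebo. Each is given for 12 weeks, with no washout between cycles. Amiloride is not in any sequence. The Introduction places it last: "offering this treatment as an open-label run-out to all patients after completion of the prospective randomised treatment cycles". The section on the run-out phase says that "the run-out phase of the study was used to evaluate the BP-lowering effectiveness of amiloride using an open label design" and describes no placebo or parallel group. It adds "Patients were evaluated at study sites at 6 and 12 weeks", with blood pressure measured as in the main study. Patients whose potassium reached 5.5 mmol/L or more during the cycles do not enter.

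**Intended use.** The Introduction says that the trial will obtain "prospective, sequential comparative evidence for amiloride in resistant hypertension by offering this treatment as an open-label run-out to all patients". The Discussion (Evaluating further diuretic therapy) gives the aim as "to determine if this replicates the effects of spironolactone on BP".

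**Stated analysis.** The Statistical analysis plan section has one sentence on amiloride: "We will examine the proportion of patients controlled by each drug who are also controlled by the run-out treatment, amiloride".

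**Time.** On the mixed model, the Statistical model section says: "The model will also include terms for treatment and phase (to allow for period effects". The list of strengths and limitations does not mention the position of amiloride in time.

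**The concern.** A crossover separates drug from time because every drug occurs in every period. That holds for the four randomised treatments. For amiloride it fails: nobody takes it in phases 1 to 4, and everyone observed in the run-out takes it in phase 5. Any change in home pressure with time in the trial is counted as an effect of amiloride. So is any effect of knowing the treatment, since most patients took the randomised drugs blinded.

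At stake is whether amiloride can be offered as a substitute for patients who do not tolerate spironolactone. The authors expect the trial to influence guidelines. A drift of a size comparable to the design difference could make amiloride look equivalent when it is not, or inferior when it is equivalent.

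The planned summary has a second weakness. It looks only at patients already controlled on the earlier drug, so its value under equal efficacy is not 100%, and the article gives no reference value for reading it.

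**Working it through.** **The article's own figure.** No sample size, test or margin is stated for amiloride. The crossover calculation uses a difference of 3 mm Hg, SD 12 mm Hg, a one-sample t test at 0.003 and 90% power. A two-sided one-sample t test gives n = 294 (power 0.901), and 294/0.85 = 345.9, rounded up to 346. Both stated figures reproduce. The SD of 12 therefore acts as the SD of a within-patient difference, which is used in step 3.

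**1. Can drug and phase be separated?** Take one patient per sequence, with columns for patient, treatment and phase.
- Phases 1 to 4: 24 + 3 + 3 = 30 columns, rank 30. All treatment contrasts are estimable.
- Add phase 5 with amiloride for all: 32 columns, rank 31. The amiloride column and the phase-5 column are identical.

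No choice of model removes this. Only an outside assumption about phase 5 does, such as a straight line through the phase effects.

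**2. Size of the shift.** Each randomised drug has mean phase (1 + 2 + 3 + 4)/4 = 2.5. Amiloride is in phase 5, so the gap is 2.5 phases. In weeks, the mean final reading is (12 + 24 + 36 + 48)/4 = 30 against week 60 if there are no breaks, a gap of 30 weeks. With a steady change of d mm Hg per phase, the shift is 2.5 × d. The article gives no drift, so d is assumed:

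| d (mm Hg per phase) | Shift (mm Hg) |
|---|---|
| 0.5 | 1.25 |
| 1.0 | 2.5 |
| 1.2 | 3.0 (the whole design difference) |
| 1.5 | 3.75 |

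Falling pressure favours amiloride; rising pressure counts against it.

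**3. What the planned share would show.** Assume home systolic pressure on each drug is normal with mean 136 and SD 12, and that control means below 135 (the threshold in the responder definition). If the within-patient difference also has SD 12, then 12 × √(2(1 − ρ)) = 12, so ρ = 0.5.
- Share controlled on one drug: Φ((135 − 136)/12) = 46.7%.
- Share controlled on both, divided by share controlled on the first, for identical drugs and no drift: about 64%.
- Under the same assumptions, shifting amiloride down by 1.25, 2.5 or 3.75 mm Hg moves 64% to about 69%, 73% or 76%. Shifting it up moves it to about 60%, 56% or 51%.
- With ρ = 0.3 or 0.7 in place of 0.5, the no-drift value is about 57% or 73%.

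**4. Blinding.** The last 100 patients were studied open-label. At the target of 346, up to 346 − 100 = 246 patients would be compared on open amiloride against blinded spironolactone.

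**The case against.** The case on the other side has several good points.

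- **The planned analysis is within-patient.** A reader might infer that amiloride is compared in different people, with poor responders lost. The stated analysis does not support that: each patient counted needs a result on both drugs. The potassium and completion rules limit to whom the result applies; they do not make the comparison one of different patients.
- **The drift is hypothetical.** A reader might infer that amiloride will be flattered. The article reports no trend, a phase term is routine in a crossover, and regression to the mean after selection at baseline would act mostly early. Neither the presence of drift nor its direction is established, so the figures above are a range of possibilities, not an estimated bias.
- **Detail may lie in documents not shown.** Silence about a phase adjustment is not a finding. The point here does not depend on that silence, because no analysis wording can separate two identical columns without an outside assumption.
- **Amiloride is peripheral.** It is not in the coprimary hierarchy, the formal objectives or the power calculation, and the article openly calls the run-out sequential and open-label. This limits the weight of the point. It does not justify the stated aim of deciding whether amiloride replicates spironolactone.
- **The remedies are imperfect.** Projecting a trend to phase 5 is untestable. Spironolactone in phase 4 covers about a quarter of patients and, with no washout described, may carry over into amiloride. Both therefore belong among sensitivity analyses.

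**Conclusion.** The point holds as a limit on what the run-out can support. Amiloride and phase 5 are completely aliased; this follows from the design and needs no assumption. The size of any resulting shift is assumed: 2.5 times the drift per phase, or 1.25 to 3.75 mm Hg in either direction for 0.5 to 1.5 mm Hg per phase, against a design difference of 3 mm Hg. The planned conditional share would be about 64% for two equally effective drugs under the stated assumptions, so a value well below 100% would not show that amiloride is worse.

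A reader might extend the concern to the main result. That is not supported: the randomised comparisons of spironolactone with placebo, doxazosin and bisoprolol are balanced over phases 1 to 4 and are unaffected.

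**What to change.** 1. Report the paired amiloride-minus-spironolactone difference in home systolic pressure, with a confidence interval, in all patients with both readings and not only those controlled on the earlier drug. If the conditional share is kept, give beside it the value expected for equally effective drugs.
2. Report the phase effects estimated from phases 1 to 4, where every treatment occurs in every phase.
3. As sensitivity analyses, show the paired difference (a) over a range of assumed phase-5 drifts, including the phase 1 to 4 trend carried forward and labelled as untestable, and (b) in patients whose spironolactone was in phase 4, where the gap is one phase. For (b), state the smaller number and the possible carry-over.
4. State that the run-out is an uncontrolled, non-randomised, open-label comparison in eligible completers, and that it cannot by itself establish that amiloride replicates spironolactone. Amend the Introduction and Discussion wording to match.

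The cost is a small extra analysis on data the trial already collects, and a more cautious statement about amiloride. Recruitment is complete, so adding amiloride to the randomisation is not proposed.

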## Methods

### Study design

PATHWAY 2 is a randomised, double blind, placebo-controlled, crossover, multicentre trial comparing the four treatment options for patients with resistant hypertension. The four treatment options are taken once daily, in addition to the maximum/best tolerated doses of three drugs at baseline according to the current NICE hypertension treatment guideline, that is, A+C+D where: A=ACE-inhibitor or Angiotensin receptor blocker; C=Calcium channel blocker; D=thiazide/thiazide-type Diuretic.^4^
^5^

After a screening visit, patients potentially eligible for randomisation proceeded to a 4-week run-in period on the patient's baseline therapy with three drugs, that is, A+C+D. After the run-in period and if still meeting the eligibility criteria, the patients were allocated double blind to a cycle of 4×once daily oral treatments in a random sequence. The randomisation is not stratified and in this 4 × 12-week period, four treatments crossover study, participants are randomised with equal probability to one of the 24 possible sequences of treatments. The treatments comprise: (1) further diuretic therapy—spironolactone; 25–50 mg, (2) α-blocker—doxazosin modified release; 4–8 mg, (3) β-blocker—bisoprolol; 5–10 mg and (4) placebo. The treatment cycles were initiated with each treatment for 6 weeks at the lower dose, followed by forced titration to twice this dose for a further 6 weeks—each cycle for a total of 12 weeks. There is no washout period between the four treatment cycles (3 active, 1 placebo), as 12 weeks of treatment per drug cycle is considered sufficient to eliminate the order effects of treatment. The total length of the trial is 52 weeks (4 weeks run-in and 4×12 week treatment cycles; figure 1).

